### Plans to promote participant retention and complete follow-up {18b}

At entry, study staff will record the phone number of one HHC in case the index patient is not reachable or changes their phone number during follow-up. For the HACF arm, visits will be scheduled at a time that is convenient for both the participant and the NTEP HCW to minimize missed follow-up visits. For the TACF arm, we will make a minimum of three attempts (at different times of day) to contact patients telephonically at each interval. The study team will meet biweekly to discuss field-level challenges, and strategies for improving retention.

### Data management {19}

This study will use electronic case report forms (eCRFs). If any data is recorded directly on the eCRF (i.e., no prior written or electronic record of data), that eCRF will be considered the source document. eCRFs will be designed using RedCap (v12.0.16) with an offline data entry option using an android mobile app. Other source documentation may include, but is not limited to, photocopies of hospital/clinic medical records, progress notes, laboratory results, and radiology results. We will use the built-in RedCap audit trail log for documenting all changes to the database during the study. All study staff will follow instructions specified in the data quality management SOP, which requires running periodic queries to check data quality.

### Confidentiality {27}

All mobile devices will be encrypted. The following procedures will be followed to protect the confidentiality of data collected and stored:Only authorized persons will be granted accessOnly authorized persons may enter and view study dataPasswords and system IDs will not be sharedPhysical security of the workstations/files will be maintainedAdequate back-up plan is in effectStaff trained on data entry system and importance of security proceduresWorkstations with databases will not be left unattended

For the qualitative data collection, audio recordings of interviews will be transcribed and audio files will be destroyed once data analysis is complete. Identifying information will be removed from transcripts and unique identification number assigned at entry will be used. Upon completion of the study, data will be stored in an on-site data storage facility for at least five years after the last participant’s follow-up is completed.

### Plans for collection, laboratory evaluation, and storage of biological specimens for genetic or molecular analysis in this trial/future use {33}

N/A. Biological specimens will not be stored.

## Statistical methods

### Statistical methods for primary and secondary outcomes {20a}

The primary analysis will be intention-to-treat, which will include all enrolled participants who have completed TB treatment and their household contacts. The primary endpoint is rate of TB disease detected by study arm, which includes recurrent TB among index cases and new TB among HHCs including children. To assess non-inferiority of TACF, compared to HACF, we will estimate a 95% confidence interval around the difference between the observed TB cases diagnosed between arms and establish non-inferiority if the upper bound of this estimate is less than 3 per 100 person-years, the non-inferiority margin. We will analyze impact of key risk factors for TB disease (tobacco smoking, biomass fuel use, alcohol use, diabetes, respiratory impairment, low socioeconomic status, catastrophic costs) on the development of recurrent TB and new TB among HHCs. We will use mixed-effects Poisson regression with random effects for HH and fixed effects for individual level variables to measure the association of key risk factors with recurrent and new TB disease in the HH. For the secondary outcome, a logistic regression model with mixed effects, to account for HH level clustering, will be used to determine if HACF is independently associated with TPT initiation among children < 6 years of age.

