#### Secondary outcome

The secondary outcome will be proportion of eligible HHCs < 6 years of age, by study arm, initiated on TPT after ruling out active TB disease. NTEP guidelines include initiation of TPT in children < 6 years of age who are contacts of a patient with TB. At enrolment, participants will report names of HHCs < 6 years of age and their history of TPT. Children who have not yet initiated TPT will be the denominator and children who initiate TPT following index patient enrolment will be the numerator. We will also measure if proportion initiating TPT differs by study arm.

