### Sample size {14}

The sample size for index patients (*n* = 1076) includes 538 in the HACF arm and 538 in the TACF arm (1:1 ratio). On average, we will enroll two HHCs per index patient (*n* = 2152). The total estimated sample size for index patients and HHCs is 3228 individuals.

Data from relevant studies suggest that 10–13% of index patients will develop recurrent TB in each arm [21, 22] and an additional 1–2% of HHCs will develop TB during the study period [58]. Assuming a rate of 12 TB cases per 100 person-years among index patients and 1 TB case per 100 person-years among HHCs, we are powered at 80% to determine that the TACF arm is non-inferior to the HACF arm with a non-inferiority interval of 3 per 100 person-years and a sample size of 1076 index patients and two HHCs per index patient (*n* = 2152). This sample size for the primary outcome is adjusted for 10% projected losses to follow-up. For the secondary outcome, we anticipate that 10% (215/2152) of HHCs will be children < 6 years of age. Data from Pune suggest that approximately 30% of child contacts will have been screened for TB and either initiated on TB therapy or TPT [59]. Thus, we anticipate 70 eligible children in each study arm and hypothesize > 60% to be screened and initiated on TB therapy or TPT in the HACF arm and less than 20% in the TACF arm. We will have at least 90% power to see a difference of 60% vs 20% and 80% power to see a difference of 50% vs 25%.

For objective 2, we will conduct a total of 40 in-depth interviews with index patients (20 with and 20 without recurrent TB) and one HHC for each patient (40 total). We will also interview 20 HCWs to achieve a total sample size of 100. We will use purposive sampling to obtain a maximum variation sample by study arm, as well as gender and age group for index patients, HHCs, and a range of HCW types and levels.

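### With about 140 eligible children, mostly one per household, the household random-effects logistic model gives an unstable odds ratio for TPT initiation; the main analysis should be the difference in proportions that the outcome and its power refer to.

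*Protocol article*

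**What the plan says.** The Secondary outcome section defines the endpoint on the scale of proportions: "The secondary outcome will be proportion of eligible HHCs < 6 years of age, by study arm, initiated on TPT". The denominator is restricted: "Children who have not yet initiated TPT will be the denominator". The section then adds a comparison without naming a method: "We will also measure if proportion initiating TPT differs by study arm".

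Sample size {14} plans 1076 index patients, hence 1076 households, with two contacts each on average. It takes 10% of the 2152 contacts (215) to be under 6 and about 30% of child contacts to have been dealt with already, and concludes "we anticipate 70 eligible children in each study arm". Power is given for 60% vs 20% (at least 90%) and for 50% vs 25% (80%).

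The analysis is set in Statistical methods for primary and secondary outcomes {20a}: "a logistic regression model with mixed effects, to account for HH level clustering". The stated purpose of this model is to test whether the home-based arm has its own association with starting preventive treatment in this age group. The article names no marginal estimator for this outcome and no fallback.

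**The concern.** A random intercept for household is estimated from agreement between children in the same household. A household with one eligible child says almost nothing about it. By the protocol's own counts nearly all contributing households have one such child, so the variance rests on very few sibling pairs.

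In a logistic model this reaches the treatment effect. The arm coefficient is conditional on the household effect, and its size grows with the household SD. An SD that cannot be pinned down therefore gives an odds ratio that cannot be pinned down, even when the two proportions are clear. The odds ratio is also a different quantity from the one the outcome and power statement describe. At stake is a published effect size, with its interval, that readers cannot relate to the proportions beside it.

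**Working it through.** **1. The plan's own figures.** Eligible children: 215 × 0.7 / 2 = 75 per arm, or 68 after a 10% loss; the plan uses 70. Power with 70 per arm, two-sided 5% (assumed, as no level is stated for this outcome), from z = [(p1 − p2)√n − 1.96√(2p̄(1 − p̄))] / √(p1(1 − p1) + p2(1 − p2)):

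- 60% vs 20%: z = (3.347 − 1.358) / 0.632 = 3.14, power 99.9% (stated: at least 90%).
- 50% vs 25%: z = (2.092 − 1.342) / 0.661 = 1.13, power 87.2%. Fisher's exact test gives 83.1%, a design effect of 1.2 gives 80.5%, and Fisher with 63 per arm (10% loss) gives 79.4% (stated: 80%).

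The power statements hold as floors.

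**2. Children per household.** 140 / 1076 = 0.130 eligible children per household. With a Poisson spread (an assumption), P(1)/P(≥1) = 94% and 1076 × P(≥2) = 8.4 households. With 150 children the figures are 93% and 9.5. If instead 40% of the 140 children (56) are in pairs, there are 28 two-child and 84 one-child households, so 84/112 = 75% still hold one.

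**3. What the model estimates.** For household SD σ, solve ∫ expit(a + σz)φ(z)dz = p in each arm; the conditional odds ratio is exp(a1 − a0).

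| Proportions | Marginal OR | σ = 1.5 | σ = 4 |
|---|---|---|---|
| 60% vs 20% | 6.0 | exp(0.572 + 1.916) = 12.0 | exp(1.109 + 3.685) = 121 |
| 50% vs 25% | 3.0 | exp(0 + 1.531) = 4.6 | exp(0 + 2.953) = 19.2 |

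The same two proportions correspond to very different odds ratios, depending on σ.

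**4. Can 140 children estimate it?** Simulation: 200 trials per scenario, 140 children, random-intercept logistic model by maximum likelihood (41-point Gauss-Hermite quadrature). Assumed inputs: σ of 0, 1.5 or 4 (latent intraclass correlation 0, 0.41, 0.83), and 13% or 40% of children in two-child households. With 13% in pairs:

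| True σ | Estimated σ below 0.1 | Estimated σ 5 or more | OR for 60% vs 20%: 5th / 50th / 95th percentile | OR for 50% vs 25%: 5th / 50th / 95th percentile |
|---|---|---|---|---|
| 0 | 50–54% | 3% | 3.7 / 7.6 / 169 | 1.9 / 3.6 / 14.5 |
| 1.5 | 19–24% | 10–13% | 4.2 / 11.2 / over 1 million | 2.0 / 5.3 / 282 |
| 4 | 0–3% | 44–51% | 7.3 / 389 / over 1 million | 2.8 / 19.1 / over 100,000 |

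Share of runs with an odds ratio above three times the marginal one, over the two effect sizes: 9–14% (σ = 0), 30–35% (σ = 1.5), 61–81% (σ = 4). With 40% in pairs: 4–6%, 20–30%, 64–89%.

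The σ = 0 row isolates instability, since there the conditional and marginal odds ratios coincide. For 60% vs 20% the crude odds ratio from the same data had a 95th percentile of 11.5, against 169 from the mixed model.

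**5. Comparator on the same data.** Difference in proportions with household-robust variance, across all σ and both pair shares:

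| | Difference in proportions | Mixed model, likelihood-ratio test |
|---|---|---|
| 60% vs 20% | median 0.40, 5th–95th percentile about 0.24–0.53; power 0.99–1.00 | power 0.98–1.00 |
| 50% vs 25% | median 0.23–0.26, 5th–95th percentile about 0.10–0.41; power 0.80–0.90 | power 0.81–0.89 |
| No difference (40% in both arms) | type I error 0.05–0.09 | type I error 0.04–0.07 |

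With 200 runs, the simulation standard error of a 5% rate is √(0.05 × 0.95 / 200) = 0.015.

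**The case against.** The best defence is that the model does the job it is given. Its stated purpose is to establish whether home-based case finding is associated with TPT initiation, and the likelihood-ratio test does that: type I error 0.04–0.07, and power close to the robust comparison. This stands. A reader might infer that the test is invalid or the outcome underpowered; neither follows. Only the likelihood-ratio version was checked, and the article does not say which test will be used.

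Second, part of the gap from the marginal odds ratio is non-collapsibility, not error. At σ = 1.5 the median estimate of 11.2 is close to the true conditional value of 12.0. This also stands, and at σ = 4 it explains most of the excess over three times the marginal value. It does not explain the σ = 0 results or the upper tails at σ = 1.5.

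Third, a reader might infer that the trial will generally report an odds ratio many times the marginal one. The documents do not support that. For 60% vs 20%, simulated medians of 84 and 99 arise if siblings are assumed to share the decision 80% of the time (90% and 70% single-child households respectively). At 50% sharing, with 90% single-child households, the median is 9.7. The protocol gives neither agreement nor sibling share. Household-level contact makes agreement plausible, but that is an inference.

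Fourth, the proportions by arm are already promised, so a clear difference would not be hidden. True, but no inferential method is attached to that promise.

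Fifth, a convergence fallback is commonly left to the analysis plan, which is not shown. Accepted: the point concerns the method the article fixes, not missing detail.

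**Conclusion.** The concern holds for the effect estimate and, by extension, its interval. It does not hold for the test of no difference or the stated power. On the protocol's own counts the household variance is weakly identified: roughly 93% of contributing households have one eligible child if children are spread at random, and 75% even if 40% of children are in pairs. The odds ratio can then be several times the marginal one. It was above three times in 4–14% of simulated trials with no household effect and in 20–35% at σ = 1.5.

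These sizes rest on the assumed σ and sibling share. The extreme upper percentiles are imprecise and depend partly on the cap on the SD in the fit (about 15); a further set of 100 runs per scenario put the 95th percentile with no household effect at 60 to 80. Interval width was not simulated directly; its instability is inferred from that of the SD and odds ratio.

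Separately from the simulation, a household-conditional odds ratio does not match an outcome defined as "proportion of eligible HHCs < 6 years of age, by study arm" and powered on proportions. This is a worthwhile, inexpensive improvement to a secondary analysis, not a threat to the trial.

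**What to change.** Name the difference in proportions between arms as the main secondary analysis, with a confidence interval from household-clustered robust standard errors. A marginal (GEE) logistic model with the same variance is an acceptable alternative. Because the robust test ran at 0.05–0.09 under no difference, add a small-sample correction to the robust variance. Keep the mixed-effects logistic model as a sensitivity analysis, reporting its estimated household SD and the number of households with two or more eligible children.

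The cost is a wording change in the protocol and analysis plan, with no new data or visits. The downside is that the effect becomes population-averaged rather than household-conditional, which is the scale on which the outcome is already defined. The adjustment for household clustering that the plan intends is kept.

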### Interim analyses {21b}

Intervention allocation will remain concealed for any interim analyses conducted.

### Methods for additional analyses (e.g., subgroup analyses) {20b}

#### Objective 1: additional analyses

Subgroup analyses will be conducted to further explore our primary and secondary outcomes. For example, as TPT is now recommended for all HHCs in India [8], we will expand upon our secondary outcome to assess proportion of HHCs (regardless of age) who initiate TPT after ruling out TB disease, by study arm.

#### Objective 2: analyses

##### Mixed-methods approach and thematic analysis

Our approach to the qualitative data will involve thematic analysis and employ both inductive and deductive coding techniques [79]. The software MAXQDA software will be used to code the textual data. We will first develop an *a priori* code book that reflects key analytic concepts and additional codes may be added to document emerging themes of interest. Textual analysis will proceed by first exploring broad patterns and experiences of study participants and then assessing possible similarities and differences in experiences between sub-groups. Quantitative data from the structured close-ended questions will be analyzed using descriptive statistics, characterizing the median and distribution of scores by sub-groups. We will integrate findings from qualitative and quantitative analyses to gain an in-depth understanding of implementation outcomes with a focus on adoption and acceptability.

##### Reach

We will use descriptive statistics to determine the proportions of socio-demographic groups that (a) receive the intervention as planned, and (b) are diagnosed with TB. We will use mixed effects logistic regression or log-binomial regression, including clinic as a mixed effect, to assess for associations between service receipt (e.g., home visit or telephone call) and the factors of interest. We will use mixed effects logistic regression to assess associations with recurrent TB diagnosis among the index patient and, separately, TB diagnosis among HHCs.

##### Implementation

We will quantitatively assess indicators of implementation fidelity including (a) whether telephone contact numbers correct and available, (b) proportion of HHs respond to phone calls, and (c) proportion of HHs located and visited. We will use a goal of 90% delivery of components considered core and able to be controlled by the health system. If a lower level of delivery is achieved in any of these components, we will explore potential reasons in in the open-ended interview segment.

### Objective 3 analyses

#### Model for recurrence and care-seeking

Our model will simulate HHs of former patients with TB, basing HH size and demographics on participating trial HHs. The probabilities of TB recurrence and of new cases among HHCs at each time step will be modeled as a parametric (inverse Gaussian) function of time since index patient treatment (with a second peak of TB risk for contacts following any recurrent TB in the HH), and care seeking probability will be a function of an individual’s time with TB symptoms. Starting with prior estimates informed by existing literature, parameters reflecting cumulative TB risk, distribution of time to TB onset, and time to diagnosis once symptomatic will be calibrated to trial data, using a Bayesian process to select estimates that most closely and consistently replicate trial results while remaining consistent with known TB epidemiology. Data from the trial that will be used for calibration include the total numbers of (a) recurrent TB cases and (b) TB among HHCs diagnosed during each 6-month follow-up interval, (c) the numbers detected at each screening visit for each arm (corresponding to individuals who are symptomatic but undiagnosed at 6 months or 12 months in the model), and the duration of symptoms reported (d) by those cases who are detected through ACF and (e) by those who were found through routine care (as reported at each study visit or detected through NTEP registry review).

Additional components of the model—including the treatment of recurrent and household TB once detected, the outcomes of undiagnosed TB, and the impact of TPT if delivered—will be based on our experience with Markov modeling of other TB-related interventions [80–84]. Among children, we will model the TPT coverage reported before the trial, and for ACF interventions, we will include the additional TPT coverage delivered during the trial, with resulting reduction in subsequent TB risks. The model will be extended over a lifetime time horizon, for purposes of comparing over simulated lifetimes the number of TB cases averted, deaths averted, years of life lost averted, and years of life with disability averted by different ACF strategies.

#### Modeling population impact of ACF interventions

We will use a population-level model to estimate the impact of each ACF strategy on TB incidence. Our model will integrate (a) estimated reductions in time spent with infectious TB in a Markov model of HACF and TACF, (b) the estimated proportion of TB in India occurring among former TB patients [21, 85], and (c) the relative number of TB transmission events generated within versus outside of an index patient's household in order to estimate resulting reductions in force of infection [86, 87]. Our dynamic transmission model will be calibrated to India’s current TB epidemic, similar to others we have previously developed [84, 88], to estimate the reduction in TB incidence that could be achieved through 10 years of widespread implementation of TACF or HACF.

#### Exploring variations on trial interventions

We will also use our Markov model of HACF and TACF described above to simulate alternative schedules and more targeted applications for those interventions. Simulated schedules may include shifting the screening visits to earlier (e.g., 3 and 6 months) or later (e.g., adding a third visit at 18 months). We will use study data on the distribution of risk factors and the associated relative risks for recurrent and household TB in the Indian population to simulate strategies which target ACF to high-risk patients.

#### Cost analyses

Intervention costs will be categorically assessed to include costs of the implementation stages of the respective intervention [73]. All costs will be assessed in units of current-year US dollars, with capital assets, up-front costs (e.g., implementation costs), and other fixed costs annuitized using a 3% annual discount rate (varied between 0 and 7% in sensitivity analyses), and each item’s relevant expected useful life years. The primary outcome for health systems cost will be average cumulative per-household cost of each ACF strategy. This estimate will include combined costs of the process of intervention implementation and delivery. We will also describe major cost drivers for each strategy and conduct sensitivity and scenario analyses around the major factors influencing the primary cost estimate. For patient and household-level factors, we will use multivariable regression techniques to develop cost functions that describe the relationships between patient and household-level variables (e.g., gender, distance from clinic, duration of smoking) and patient costs under each intervention condition. For patient costs, the primary outcome will be assessed as total economic cost per household with index TB patient, categorically assessed by the type of TB episode(s) experienced (initial, recurrent, and/or new). We will also calculate the percentage of TB illness related economic costs out of the household income to assess whether the index patient’s household experienced catastrophic costs (defined as TB related patient costs exceeding 20% of the household income) [74, 89].

#### Cost-effectiveness

Both incremental costs and effectiveness will be estimated relative to no intervention primarily and for HACF relative to TACF secondarily. Cost-effectiveness will first be determined based on empiric cost estimates of the respective strategies and the primary outcome assessed in objective 1. Therefore, the primary cost-effectiveness outcome will be assessed as incremental cost (whichever strategy has higher effectiveness) per additional TB episode (new or recurrent) identified through the intervention.

The secondary measure of cost-effectiveness will be the incremental cost per incremental DALY averted. DALYs averted will be based on estimated numbers of TB cases prevented, improved treatment outcomes, and deaths averted using disability weights from the 2017 Global Burden of Disease study [90, 91]. Cost-effectiveness will be evaluated from the health system perspective over a lifetime time horizon, with future costs and effectiveness discounted at 3% annually. The incremental cost-effectiveness ratio will be calculated comparing HACF and TACF versus the standard of care (no ACF), comparing different ACF schedules for ACF strategies which appeared cost-effective, and considering the cost-effectiveness of targeted ACF (based on identifiable risk factors in the index patient) for strategies that do not appear cost-effective when delivered to all former TB patients. Accepted methodological guidelines will be followed for the conduct, and reporting of the cost-effectiveness analysis [92–94].

